## Trial conduct

### Consent

All patients in ICU who are clinically judged to have severe sepsis will be screened against the inclusion and exclusion criteria. Informed consent will be obtained prior to enrolling patients into the trial. In most cases it will not be possible to obtain prospective consent from the patient due to a lack of capacity as a result of their critical illness and its treatment. Under such conditions, written informed consent will be sought from the patient’s personal legal representative (PerLR) who will be provided with a copy of the Patient Information Sheet (PIS). If the patient lacks capacity and there is no PerLR then a doctor, unconnected with the trial, may act as a professional legal representative (ProLR) and provide consent for enrolment into the trial. All surviving patients will be informed about the trial once they regain capacity and will be asked to give consent to their ongoing involvement in the trial.

### Randomization and supply of study drug

Orion Corporation (Espoo, Finland) is providing the study drugs for the trial. Levosimendan 12.5 mg/5 mls vials and identical placebo will be supplied to Victoria Pharmaceuticals (Belfast, UK) who will be responsible for packaging, labelling, and distributing the drugs to study sites in accordance with Medicines and Healthcare products Regulatory Agency (MHRA) requirements.

Randomization will be by computer generated randomized numbers and will use an online system (InForm™, Oracle Corp, California, United States). Randomization will be stratified by ICU and will occur on a 1:1 basis in permuted blocks.

### Administration of study drug

Patients will be randomized to receive an intravenous infusion of levosimendan at 0.05 to 0.20 μg.kg^−1^.min^−1^ or placebo for a period of 24 hours. The infusion will be prepared by diluting the contents of one vial of study drug in 500 ml of 5% dextrose. The study drug will not be started until the treating clinician is confident that adequate fluid resuscitation has been achieved and that the patient has reached their target blood pressure; this may be a mean arterial pressure (MAP) of 65 to 70 mmHg but may be increased or reduced if the treating clinician feels this is clinically necessary. The infusion will then be commenced at a rate of 0.1 μg.kg^−1^.min^−1^ based on actual (estimated) body weight. Although the summary of product characteristics states that an initial bolus of levosimendan should be given, in this trial the bolus dose will not be given to avoid hypotension and maintain patient safety. After 2 to 4 hours the infusion will be increased to 0.2 μg.kg^−1^.min^−1^ for the remaining 20 to 22 hours if there is no significant hypotension or tachycardia. Any initial hypotension will be treated with a fluid challenge and an increase in vasopressor dose if needed. Throughout the duration of the infusion, clinicians will have the option to reduce the infusion or stop it if they deem there to be significant hypotension or tachycardia. Details of the study drug infusion protocol are shown in Figure 2. Titration of the study drug dose between 0.05 and 0.2 μg.kg^−1^.min^−1^ will ensure patients receive an effective dose whilst minimizing adverse effects.

**Figure 2 F2:**
[figure not shown]
**LeoPARDS blinded study drug infusion management guideline.** HR, Heart rate; MAP, Mean Arterial Pressure. ⬆ = increased.

### General patient management and treatment

Patients will receive all normal standard care and be managed in accordance with current accepted best practice as recommended by the Surviving Sepsis Campaign (SSC) guidelines [47]. Crystalloid solutions will be used for intravenous fluid resuscitation. Gelatin-based or human albumin solutions may be used as alternative resuscitation solutions. Norepinephrine is the initial vasopressor of choice. This should be titrated to a target MAP of 65 to 70 mmHg or as deemed appropriate by the treating clinician. Vasopressin, or any of its analogues, may be used as an alternative vasopressor or in addition to norepinephrine. The lowest dose of vasopressor that maintains a MAP that provides acceptable tissue perfusion should be used. Additional inotropic drugs may be used as clinically indicated. Dobutamine is the inotropic agent of choice but others, such as epinephrine or milrinone, may be used. A central venous saturation (S_cv_O_2_) of more than or equal to 70% should be targeted in the early stages of septic shock management. Dobutamine (or any other inotropes) should be titrated down and weaned off once an adequate oxygen delivery is achieved. Hydrocortisone should only be used for patients who are poorly responsive to vasopressors, as per the SSC guidelines [47]. Low doses, such as 200 mg hydrocortisone administered intravenously daily in divided doses or by infusion, should be used and weaned off once shock resolves.

A lung-protective strategy should be used: target tidal volume 6-ml.kg^−1^ ideal body weight, limiting plateau pressure to ≤30 cmH_2_O, accepting permissive hypercarbia, and ensuring adequate levels of positive end-expiratory pressure (PEEP). High frequency oscillation, neuromuscular blockade, inhaled nitric oxide, prone positioning, and extra-corporeal membrane oxygenation are all permitted as needed for the management of refractory hypoxemia. Continuous veno-venous hemo(dia)filtration is the renal replacement therapy of choice, however, other modalities such as intermittent hemodialysis may be used since there is no clear evidence that one modality is superior [48]. High volume hemofiltration solely for the treatment of sepsis in the absence of renal failure should not be used.

### Pharmacovigilance & patient follow-up

An assessment of the safety of levosimendan is an important outcome measure for the LeoPARDS trial. Given that the trial is being conducted in critically ill patients, a significant number of patients are likely to experience adverse events (AEs). Events that are in keeping with the patient’s clinical condition will not be reported as AEs. The following clinical outcomes from sepsis will not be recorded as AEs unless the local investigator deems the event to be related to the study drug or the protocol: death, cardiovascular failure, respiratory failure, hepatic failure, renal failure, and hematological failure. Specific information about the occurrence of a myocardial infarction or acute coronary syndrome and life-threatening arrhythmias will be recorded in the case report form. All adverse events will be assessed for likely relationship to the study drug. All serious adverse event (SAE) or a suspected unexpected serious adverse reaction (SUSAR) will be reported to the trial coordination centre within 24 hours and to the relevant authorities in accordance with current regulations.

Patients will be followed up on daily whilst on the ICU. Routinely collected clinical data (cardiovascular, respiratory, and renal physiological variables as well as hematological and biochemical blood test results) will be recorded on a daily basis during this time using the electronic case report form. Patients will also be followed up to ascertain survival status at 28 days post-recruitment, at hospital discharge, and at 3 and 6 months post-recruitment using The Health and Social Care Information Centre.

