### Risks

Levosimendan has been widely used in patients with acute heart failure with a good safety profile and no known significant pharmacokinetic drug interactions. According to the levosimendan investigators’ brochure, between September 2000 (when the drug first received a license in Sweden) and November 2010 an estimated 440,000 patients have received the drug with a reported serious adverse drug reaction rate of 791 out of 440,000 (0.2%). The most common adverse events reported were hypotension (0.03%) and serious arrhythmias (0.02%). Levosimendan has also been used in over 200 patients with septic shock in published controlled trials and case series without any reported significant adverse effects. Adequate cardiovascular resuscitation with intravenous fluids and norepinephrine, as well as avoiding both the initial bolus loading dose and a high-dose infusion (≥0.4 μg.kg^−1^.min^−1^) help reduce adverse effects when used in sepsis [35]. Levosimendan is currently used in many ICUs within Europe in the treatment of severe sepsis and septic shock and has recently been recommended as an alternative inotrope in the German Sepsis Society guidelines [36].

There is therefore good evidence that levosimendan improves cardiac output, regional perfusion, and other physiological endpoints, including renal function, in patients with septic shock. This trial is therefore designed to identify important clinical outcome benefits and to further explore the mechanisms of action of levosimendan in septic shock.

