## Methods/Design

The Levosimendan for the Prevention of Acute oRgan Dysfunction in Sepsis (LeoPARDS) trial is a multicenter prospective, randomized, double-blind, parallel group, placebo-controlled trial. The trial is sponsored by Imperial College London (United Kingdom) and coordinated by the Imperial Clinical Trials Unit. The trial will be conducted in accordance with the principles of the Declaration of Helsinki and Good Clinical Practice and is approved by the independent National Research Ethics Committee London - Harrow (13/LO/0365). It is registered on the European Union Drug Regulating Authorities Clinical Trials database (EudraCT 2012-005159-18) and the International Standardised Randomised Controlled Trial Registry (ISRCTN12776039). The study is funded by the Efficacy and Mechanism Evaluation (EME) program of the National Institute for Health Research (United Kingdom)

The primary objectives of the trial are as follows: (1) to ascertain if levosimendan reduces the incidence and severity of organ dysfunction compared to placebo in adult patients who have septic shock; (2) to identify the effect of levosimendan on individual organ function in septic shock; and (3) to establish the safety profile and pharmacokinetics of levosimendan in this group of patients.

The secondary objectives of the study are: (1) to identify whether levosimendan reduces the need for and duration of catecholamine support and thus reduces myocardial injury; (2) to establish whether levosimendan alters the pro- and anti-inflammatory balance in sepsis; and (3) to collect long-term (3 and 6 month) survival data to help inform the appropriate long-term outcome measure for a subsequent effectiveness trial, should the efficacy of levosimendan be confirmed in this phase IIb trial.

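### The adverse-event rule lets hypotension and non-life-threatening tachyarrhythmia go uncounted, although both are named safety concerns of the study drug and safety is part of a primary objective

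*Protocol article*

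**What the plan says.** Under Methods/Design, the third primary objective is "to establish the safety profile and pharmacokinetics of levosimendan in this group of patients". Pharmacovigilance & patient follow-up repeats the priority: "An assessment of the safety of levosimendan is an important outcome measure for the LeoPARDS trial".

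That section then sets three separate rules:

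- **General exclusion.** "Events that are in keeping with the patient’s clinical condition will not be reported as AEs". This sentence carries no exception for events thought to be related to the drug.
- **Listed outcomes.** Six outcomes, "death, cardiovascular failure, respiratory failure, hepatic failure, renal failure, and hematological failure", "will not be recorded as AEs unless the local investigator deems the event to be related to the study drug" or to the protocol.
- **Recorded regardless.** Information on "myocardial infarction or acute coronary syndrome and life-threatening arrhythmias will be recorded in the case report form", with no condition on attribution.

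Elsewhere, Risks gives hypotension (0.03%) and serious arrhythmias (0.02%) as the most common reported adverse events. Inclusion criteria requires hypotension needing a vasopressor and lists tachycardia among the systemic inflammatory response criteria. Administration of study drug allows the infusion to be reduced or stopped for significant hypotension or tachycardia.

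**The concern.** The events most likely to be set aside as part of the disease include those the article itself ties to the drug. Every patient enters with vasopressor-requiring hypotension, and many will have tachycardia. A new or worse episode during the infusion can therefore be read as the underlying illness and left unreported, or read as cardiovascular failure and recorded only if the local investigator blames the drug or the protocol.

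In a single patient with septic shock there is little basis for saying which cause was at work. A double-blind randomised trial avoids that problem by comparing how often the event occurs in each arm, and this needs events counted whatever anyone thinks caused them. If the count depends on attribution, a real excess can shrink to a few reports per arm. The data monitoring committee is also affected: it reviews adverse-event data, and the Pharmacokinetic substudy section asks it to consider links between infusion rates, drug levels and adverse events.

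**Working it through.** **The article's own figure.** Risks gives 791 serious adverse drug reactions in an estimated 440,000 patients: 791 / 440,000 = 0.180%, which rounds to the stated 0.2%. The rates of 0.03% and 0.02% correspond to 440,000 × 0.0003 = 132 and 440,000 × 0.0002 = 88 reports. These show which harms are known. They are not event rates in septic shock and are not used as such below.

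**Which rule reaches which event.**

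| Event | General exclusion | Six listed outcomes | Recorded regardless |
|---|---|---|---|
| Hypotension needing intervention | Can apply | Can apply, as cardiovascular failure | No |
| Non-life-threatening tachyarrhythmia | Can apply | Not listed | No |
| Life-threatening arrhythmia | – | – | Yes |
| Myocardial infarction or acute coronary syndrome | – | – | Yes |
| Death | – | Yes | Survival is followed in all patients |

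The first two rows have no attribution-free event count stated for all patients.

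**What under-recording costs (illustration).** Inputs: 258 per arm (Primary outcome measure and sample size) and a two-sided 5% level. The event rates and recorded fractions are assumptions; the article gives neither. Let p0 and p1 be the true proportions with an event, and f the fraction recorded, taken as equal in both arms because of blinding. The recorded proportions are f·p0 and f·p1, and

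power = Φ( f(p1 − p0) / SE − 1.96 ), SE = √{ [f·p0(1 − f·p0) + f·p1(1 − f·p1)] / 258 }.

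For true rates of 10% and 20%:

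- f = 1: SE = √(0.2500/258) = 0.0311; 0.10/0.0311 − 1.96 = 1.25; power 0.895.
- f = 0.5 (5% v 10%): SE = √(0.1375/258) = 0.0231; 0.05/0.0231 − 1.96 = 0.21; power 0.58.
- f = 0.3 (3% v 6%): SE = √(0.0855/258) = 0.0182; 0.03/0.0182 − 1.96 = −0.31; power 0.38.
- f = 0.2 (2% v 4%): SE = √(0.0580/258) = 0.0150; 0.02/0.0150 − 1.96 = −0.63; power 0.27.

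In expected counts, 25.8 v 51.6 patients with an event (258 × 0.10 and 258 × 0.20) become 5.2 v 10.3 at f = 0.2.

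Other assumed rates show the same pattern:

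| True rates | f = 1 | f = 0.5 | f = 0.25 | f = 0.1 |
|---|---|---|---|---|
| 5% v 10% | 0.58 | 0.32 | 0.18 | 0.10 |
| 10% v 20% | 0.89 | 0.58 | 0.32 | 0.15 |
| 30% v 40% | 0.67 | 0.32 | 0.17 | 0.09 |

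Using a pooled variance for the test changes no entry by more than about 0.004.

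**The case against.** The case for the plan has real force.

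- **The relatedness clause does not name these harms.** A reader might infer that hypotension and tachyarrhythmia are both recorded only if attributed to the drug. The text does not say so. The clause governs six listed outcomes; hypotension can enter only as cardiovascular failure, and tachyarrhythmia is not on the list. This stands as a correction, but it does not rescue the plan, because the general exclusion has no exception at all.
- **Arrhythmia is partly covered.** It would be wrong to say that tachyarrhythmia as such is filtered out: life-threatening arrhythmias are recorded regardless. What is left is the non-life-threatening kind. Hypotension has no such provision.
- **Other data bear on haemodynamic harm.** Daily cardiovascular variables, the SOFA score, catecholamine-free days and survival are compared or available by arm, so death and organ failure do not depend on attribution. This also stands. However, none of these is stated to count treated hypotension or lesser tachyarrhythmia during the infusion. The pharmacokinetic substudy does look at tachycardia and hypotension, but in the first 80 patients (about 40 on active drug at 1:1) and against drug levels, not as a comparison of all randomised patients.
- **Daily recording may be enough.** One might infer that once-daily values will miss short episodes. The article says only that variables are recorded daily, not whether as single or worst values. They may miss such episodes; that they will is not shown.
- **Exempting expected outcomes is common in critical care, and case-report-form detail belongs in the full protocol.** Exemption is reasonable where the outcome is captured elsewhere, as death and renal failure are here. The point rests on an exclusion rule that the article states, not on detail it omits. The full protocol and the infusion guideline (Figure 2) are not shown and may already provide for these events.

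**Conclusion.** The concern holds for hypotension and for non-life-threatening tachyarrhythmia. As written, the exclusion rules can remove both from adverse-event counts, and the article states no attribution-free count of them in all patients, so the arm comparison of these harms is likely to be under-ascertained. On assumed rates of 10% v 20%, power falls from about 89% with full recording to 58% at half and 27% to 38% at 20% to 30%. Those figures assume equal recording in both arms and that recorded adverse events are the only source for the comparison. The partial data described above soften the second assumption.

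Because the trial is double-blind, the expected effect is lost events and lost power rather than a clear bias in one direction, although visible haemodynamic effects could partly unblind investigators. A reader might go further and conclude that the safety objective cannot be met. The article does not support that: survival, organ function and the most serious cardiac events are captured regardless of attribution. This is a worthwhile correction to the safety plan, held with moderate confidence because the full protocol is not shown.

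**What to change.** In Pharmacovigilance & patient follow-up, exempt the following from both exclusions and record them in every patient in both arms, whatever the attribution:

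- each reduction or stop of the infusion, with its reason (hypotension, tachycardia, other);
- tachyarrhythmia needing treatment;
- hypotension needing intervention during the infusion.

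Compare the counts by arm and include them in the reports to the data monitoring committee. Leave expedited reporting and infusion management unchanged.

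The cost is a few extra fields in the electronic case report form and slightly more data entry; no new assessments are needed. If the full protocol already records these events, it is enough to reconcile this section with it.

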### Statistical analysis and trial oversight

A full statistical analysis plan will be drawn up before the trial database is locked and analyzed. Prior to performing any statistical tests or fitting statistical models, an exploratory analysis of the baseline variables and outcome measures will be completed. The level and pattern of missing data in the baseline variables and outcomes will be established by forming appropriate tables and likely causes of any missing values will be investigated. Any issues will be dealt with using standard statistical techniques. The primary analyses will be carried out on an intention-to-treat basis. The Trial Steering Committee (TSC) with an independent chair and a majority of independent members including patient and public representatives will be responsible for overseeing the progress of the trial and will meet six-monthly. The independent DMEC will meet six-monthly to review ongoing recruitment, protocol compliance, clinical outcome, and adverse event data. They will provide the TSC with written reports advising about ongoing trial conduct.

The trial will end once 516 patients have been enrolled, all patients have completed 6 months follow-up and the database is locked.

## Discussion

There is good evidence from pre-clinical studies [19-23], case series [24-27], and small clinical trials [28-33] looking at physiological endpoints that levosimendan may have a beneficial role in the management of septic shock. Its mechanism of action as a calcium sensitizer means it has theoretical advantages over other inotropic drugs, including less increase in myocardial oxygen demand and reduced rates of arrhythmias. It may also improve peripheral organ perfusion and have anti-inflammatory properties.

This trial will test the clinical efficacy of levosimendan to reduce acute organ dysfunction in adult septic shock and will also examine its safety profile in this patient group. The primary outcome measure (mean SOFA score) allows an overall assessment of the effect of the drug on organ function which is known to correlate with survival. However, as a composite score it is vital to examine each organ system separately to fully understand the biological effect of levosimendan. The collection and analysis of blood and urine samples will also allow a fuller examination of its biological effects.

## Trial status

The trial is due to open for recruitment in January 2014. Recruitment of all 516 patients is expected to take 30 months.

## Abbreviations

AE: Adverse Event; AKI: Acute Kidney Injury; AKIN: Acute Kidney Injury Network; AUC: Area Under the Curve; BNP: B-type Natriuretic Peptide; Cmax: Maximum (peak) concentration; CPAP: Continuous Positive Airway Pressure; CCMDS: Critical Care Minimum Data Set; CVC: Central Venous Catheter; DMEC: Data Monitoring and Ethical Committee; ICU: Intensive Care Unit; MAP: Mean arterial pressure; NGAL: Neutrophil Gelatinase-Associated Lipocalin; PEEP: Positive End-Expiratory Pressure; PerLR: Personal Legal Representative; PIS: Patient Information Sheet; ProLR: Professional Legal Representative; SAE: Serious Adverse Event; ScvVO2: Central Venous Oxygen Saturations; SD: Standard Deviation; SOFA: Serial Organ Failure Assessment; SSC: Surviving Sepsis Campaign; SUSAR: Suspected Unexpected Serious Adverse Reaction; TSC: Trial Steering Committee; VASST: Vasopressin And Septic Shock Trial.
